1. STUDY POPULATION
   1. Population (base)

Healthcare professionals (i.e. general practitioners, practice nurses, medical assistants) from primary care practices and patients with T2DM will be included in this study. To recruit practices and patients, we collaborate with the primary care group ‘Huisarts & Zorg’, a provider network of 75 general practices in the region of Gorinchem (a municipality in South Holland). This established collaboration enhances the likelihood of successful recruitment of primary care practices for this pilot study. Four primary care practices from care group ‘Huisarts & Zorg’ will be included in this pilot study. Healthcare professionals from participating primary care practices will be asked to recruit adult patients with T2DM. Recruiting patients through their healthcare professionals is anticipated to increase the likelihood of study participation. Patients will be enrolled in the study after receiving face-to-face and written information about the research and after giving written informed consent (see section 11.2 for detailed information).

- 1. Inclusion criteria

In order to be eligible to participate in this study, a subject must meet all of the following criteria:

- Is diagnosed with T2DM
- Eighteen years or older
- Need to decide on T2DM treatment based on the NHG guideline
- Multiple treatment options (medication and/or lifestyle) are possible as judged by the HCP
- Speak Dutch at a necessary level to complete questionnaires and ensure involvement in SDM

To be able to recruit a diverse population of patients with T2DM, we will select general practices that differ in terms of the sociodemographic background of their patient panels.

- 1. Exclusion criteria

A potential subject who meets any of the following criteria will be excluded from participation in this study:

- Severe cognitive impairments that hamper SDM
  1. Sample size calculation

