Primary outcomes include patient decisional conflict, level of SDM as perceived by patients and HCPs, and patient knowledge. Decisional conflict is measured using the 16-item Decisional Conflict Scale for patients [37]. Patients will be asked to reflect on the treatment decision they made with their HCP and respond to 16 statements in the DCS using a five-point Likert scale (ranging from completely agree to completely disagree). Besides a total score, the DCS includes five dimensions (i.e. information, support, clarification or values, certainty, and decision quality) with higher scores on a five-point scale indicating more decisional conflict. Patient-rated level of SDM is measured by the 3-item CollaboRATE survey and the SDM-Q-9 questionnaire. The CollaboRATE survey assesses patients’ perception of being informed and engaged in the decision-making steps on a scale of zero (no effort was made) to nine (every effort was made) [38, 39]. The SDM-Q-9 questionnaire measures the extent of SDM during a consultation between the patient and HCP [40]. This questionnaire consists of nine statements each describing a different step of the SDM process. All items are scored on a six-point Likert scale from zero (completely disagree) to five (completely agree). The questionnaire also includes two open-ended questions on what health problem was the subject of the consultation and which decision was made. The SDM-Q-Doc questionnaire (SDM-Q-9 adapted to the HCP viewpoint) is used to measure the level of SDM during a consultation from the perspective of a HCP [40]. Patient knowledge is measured with nine tailor-made multiple-choice questions assessing patients’ understanding of the (risks and benefits of) glucose-lowering treatments.

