| Health-related quality of life | Patient | Dutch EuroQol (EQ) 5D-5L (quality of life) | The EQ 5D-5L assesses quality of life and includes the EQ-5D dimension and the EQ visual analog scale (VAS). EQ-5D comprises five dimensions: mobility, self-care, usual activities, pain, and anxiety. Each dimension of the EQ-5D is scored on a five-point Likert score (from no problems to extreme problems). The EQ VAS is used to assess the patient’s self-reported health on a visual analog scale. |

*Timeline*

The schedule of study enrolment and assessment can be found in Table 2. There are some differences in the timeline between participating patients in the intervention practices and control practices.

- - - - Intervention practices

Baseline measurements will capture sociodemographic and clinical patient characteristics, patient knowledge, glycemic control, medication adherence, costs, and health-related quality of life. Patients complete the DCS, CollaboRATE survey, and SDM-Q-9 questionnaire directly following the clinical encounter where a treatment decision is made.

- - - - Control practices

Patients will complete all questionnaires (sociodemographic and clinical characteristics, patient knowledge, glycemic control, medication adherence, costs, and health-related quality of life) directly following the clinical encounter where a treatment decision is made.

For both study arms, HCPs complete the SDM-Q-Doc questionnaire directly following the clinical encounter where a treatment decision is made. Follow-ups at 3 months and 9 months will facilitate the measurement of glycemic control, medication adherence, costs, and health-related quality of life. Semi-structured interviews with patients will be held within 1 month after study participation and the focus groups with HCPs from participating practices will be held at the end of the 9 months of implementation.

**Table 1.** Schedule of study enrolment and assessment.

|  |  | Enrolment |  |  |  |  |
| --- | --- | --- | --- | --- | --- | --- |
| Time point |  |  | t0 | t1 | t2 | t3 |
| Enrolment | Eligibility | x |  |  |  |  |
|  | Informed consent | x |  |  |  |  |
| Patient assessment (intervention) | Sociodemographic and clinical characteristics |  | x |  |  |  |
|  | Decisional Conflict |  |  | x | x | x |
|  | Patient-rated level of SDM |  |  | x | x | x |
|  | Patient knowledge |  | x |  |  |  |
|  | Medication adherence |  | x |  | x | x |
|  | Glycemic control |  | x |  | x | x |

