|  | Costs |  | x |  | x | x |
|  | Health-related quality of life |  | x |  | x | x |
|  | Semi-structured interviews with patients |  |  | x |  |  |
| Patient assessment (control) | Sociodemographic and clinical characteristics |  |  | x |  |  |
|  | Decisional Conflict |  |  | x | x | x |
|  | Patient-rated level of SDM |  |  | x | x | x |
|  | Patient knowledge |  |  | x |  |  |
|  | Medication adherence |  |  | x | x | x |
|  | Glycemic control |  |  | x | x | x |
|  | Costs |  |  | x | x | x |
|  | Health-related quality of life |  |  | x | x | x |
|  | Semi-structured interviews with patients |  |  | x |  |  |
| HCP assessment | HCP-level of SDM |  |  | x |  |  |
|  | Focus group with HCPs |  |  |  |  | x |

t0 = baseline measurement; t1 = directly following the clinical encounter where a treatment decision is made; t2 = 3-month follow-up; t3 = 9-month follow-up. SDM: shared decision-making, HCP: healthcare professional.

All questionnaires (added as separate documents to the research protocol) will be included in the digital platform of PatientPlus. Participating patients and HCPs from the intervention practices will have an account giving them access to the PatientPlus platform. Patients and HCPs from the intervention practices are asked to complete the questionnaires via the online platform of PatientPlus. After 3 and 9 months, the patient will receive automatic notifications (via mail) prompting them to complete the follow-up questionnaires. Additionally, automated reminders will be sent if the patient has not yet completed the questionnaire.

Patients and HCPs from the control group will not have an account on the PatientPlus platform to avoid bias. They will complete questionnaires via Qualtrics [45]. After 3 and 9 months, the patient will receive automatic notifications (via mail) prompting them to complete the follow-up questionnaires. Additionally, automated reminders will be sent if the patient has not yet completed the questionnaire.

- 1. Withdrawal of individual subjects

Subjects can leave the study at any time for any reason if they wish to do so without any consequences. The investigator can decide to withdraw a subject from the study for urgent medical reasons.

- - 1. Specific criteria for withdrawal (if applicable)

Not applicable.

- 1. Replacement of individual subjects after withdrawal

Not applicable.

- 1. Follow-up of subjects withdrawn from treatment

Not applicable.

- 1. Premature termination of the study

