We request that patients fill out questionnaires at three (control group) or four (intervention group) time points spanning 9 months: at the onset of participation, after 3 months, and at 9 months. These questionnaires are accessible through the PatientPlus online platform or Qualtrics (depending on whether the patient/HCP is in the intervention or control group). For the intervention group, the initial questionnaire comprises two parts, with part 1 being completed after signing the informed consent, taking approximately 5-10 minutes. Subsequently, upon making a treatment decision for type 2 diabetes with their healthcare provider, patients proceed to complete part 2, which requires around 15-25 minutes. Patients in the control group will complete part 1 and part 2 of the questionnaires at the same time (i.e. after the consult where a treatment decision was made). Automated reminders prompt patients to complete subsequent questionnaires after 3 and 9 months, each requiring approximately 5-10 minutes for completion.

Patient questionnaire responses will remain confidential and inaccessible to healthcare providers, ensuring the privacy of the patients. The interviews are optional for patients. When signing the informed consent, they have the option to indicate whether they grant permission for researchers to contact them for an interview. During the interviews, participants will be asked about the readability and understandability of the questionnaires. Thus, the study does not affect the mental integrity of the participants. Moreover, the study requires limited involvement of patients and therefore imposes no burden.

In summary, participating patients will have the opportunity to contribute to advancements in the field of person-centered care for the treatment of T2DM. The careful design of the study ensures the safety and well-being of the participants. The scientific and societal benefits of their involvement underscore the importance of this research in advancing the understanding and practice of person-centred care in the context of T2DM.

- 1. Compensation for injury

The sponsor has a liability insurance which is in accordance with article 7 of the WMO.

The sponsor (also) has an insurance which is in accordance with the legal requirements in the Netherlands (Article 7 WMO). This insurance provides cover for damage to research subjects through injury or death caused by the study.

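### The t1 assessment waits for a treatment decision, so patients who reach none have no t1 scores, and undecided controls never supply baseline characteristics or knowledge

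*Protocol*

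**What the plan says.** **Entry.** Protocol section 4.2 admits patients who "Need to decide on T2DM treatment based on the NHG guideline". A decision need not have been reached.

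**Trigger for t1.** The footnote to the schedule of enrolment and assessment (section 8.3) reads "t1 = directly following the clinical encounter where a treatment decision is made". The timeline text for intervention practices agrees: "Patients complete the DCS, CollaboRATE survey, and SDM-Q-9 questionnaire directly following the clinical encounter where a treatment decision is made". The same text gives control patients and the professionals' SDM-Q-Doc the same trigger. Section 11.4 says that "upon making a treatment decision for type 2 diabetes with their healthcare provider, patients proceed to complete part 2".

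**Baseline.** The arms differ. Intervention patients have a t0, with "part 1 being completed after signing the informed consent, taking approximately 5-10 minutes". For controls, "Patients in the control group will complete part 1 and part 2 of the questionnaires at the same time", that is, after the consult in which the decision was taken. The schedule table has no t0 mark for controls.

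**Follow-up.** In both arms the table row for the main trial's primary outcome is "Decisional Conflict | | | x | x | x", which places the scale at t1, t2 and t3. The follow-up sentence in section 8.3 lists only adherence, HbA1c, costs and quality of life at 3 and 9 months. Section 8.3 also says that follow-up questionnaires are prompted automatically in both arms. It does not make them depend on t1 and does not say from which date the 3 and 9 months run.

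**The concern.** Whether a decision is reached is known only after randomisation. The program under study, with its decision aid and preparatory consult, is meant to act on that process. It is also closely tied to decisional conflict: section 8.3 lists certainty as one dimension of the scale. A t1 score taken only from patients who decided is therefore taken from a group selected on something near the outcome, and the selected share may differ by arm.

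The more concrete problem concerns objective 1. Section 8.1.1 makes sociodemographic and clinical characteristics part of the primary endpoint on recruitment and retention, and the research question is whether the sample is representative. Section 10.1 promises to describe missing-data patterns so that potential biases can be seen. Both need some information on the patients who drop out of the measurement sequence. In the control arm, the trigger withholds that information for the undecided.

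**Working it through.** **Denominator.** Section 4.4 starts from 30 patients and adds a third: 30 × (1 + 1/3) = 40, or 20 per arm. This reproduces the protocol's figure. The base of 30 comes from a cited rule that the document does not print, so only the inflation step was checked.

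**Tracing a consented patient who reaches no decision**, using the schedule table and the text of sections 8.3 and 11.4:

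| Item | Intervention, undecided | Control, undecided |
|---|---|---|
| Characteristics | collected at t0 | scheduled at t1 only: never collected |
| Knowledge | collected at t0 | scheduled at t1 only: never collected |
| First adherence, costs, quality of life | collected at t0 | scheduled at t1: missing |
| DCS, CollaboRATE, SDM-Q-9 at t1 | missing | missing |
| SDM-Q-Doc (t1 only) | missing | missing |
| 3- and 9-month questionnaires | still prompted | still prompted |
| Questionnaire time points left | 3 of 4 | 2 of 3 |

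The totals of four and three time points are those in section 11.4.

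**Decisional conflict after t1.** By the table, 2 of the 3 planned occasions remain in either arm (t2 and t3). By the follow-up sentence, none remain. The two cannot both be right. Even where the table applies, the instruction fits an undecided patient poorly: "Patients will be asked to reflect on the treatment decision they made with their HCP".

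**Late t1.** The trigger is the encounter in which a decision is made, not the first encounter. A patient who postpones and decides later therefore has a t1, but a late one. With no window, a deferring control's first measurement of everything moves later with it.

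**How many patients.** The protocol gives no share reaching no decision, so the share u below is an assumption. Expected number per arm = 20u. The chance of at least one in an arm = 1 − (1 − u)^20, which treats patients as independent. With patients grouped in two practices per arm, this is approximate.

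| Assumed u | Patients per arm without t1 | Chance of at least one among 20 |
|---|---|---|
| 5% | 1 | 64% |
| 10% | 2 | 88% |
| 20% | 4 | 99% |
| 30% | 6 | over 99% |

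No sample size or power figure in the protocol changes.

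**The case against.** Several stronger readings are tempting, and the document does not support them.

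- A reader might infer that undecided patients are never assessed for decisional conflict. The schedule table marks the scale at t2 and t3 in both arms. Only the follow-up sentence leaves it out.
- A reader might infer that undecided controls supply no questionnaire data. The 3- and 9-month questionnaires are prompted automatically. The inference would hold only if their clock started at t1, which is not stated. HbA1c from the general practitioner and pharmacy records do not depend on a questionnaire either.
- A reader might infer that retention cannot be assessed for these patients. Section 12.1 has the practices supply recruitment, retention and consent rates. What is lost is the description of who the undecided controls are, not the count.
- A reader might put a size in standard deviations on the distortion between arms. That would need assumed deferral rates for each arm and an assumed score gap, and section 10.1 rules out any effectiveness analysis in this pilot.

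Two further arguments have weight. The scale as used here asks about a decision already made, so giving it after a decision suits that construct, and adding patients with a pending decision would mix two things. Also, the decision aid always shows no treatment and lifestyle change as options (section 5.1), so declining medication can count as a decision. The affected group is therefore narrower than all who leave without a prescription. Both points stand, and they limit the size of the problem and shape the remedy.

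The commitment in section 10.1 to explore reasons for missing data helps only in part. No item records that a decision was deferred, and for undecided controls there are no questionnaire-based characteristics with which to describe the pattern.

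**Conclusion.** The point holds in a limited form. The t1 assessment depends on a decision being made, with no window and no fallback. Deferring patients are measured late. Patients who reach no decision have no t1 score for decisional conflict or shared decision-making. Because controls have no t0, their undecided patients also lack all baseline questionnaire data, and their characteristics and knowledge are never collected, while undecided intervention patients keep theirs. The control-arm description of the sample and of missing data is thus confined to deciders, and deferral goes uncounted.

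The size is unknown from the document. Under assumed shares of 5% to 30% it is 1 to 6 of 20 patients per arm. No planned result of the pilot is invalidated, since the analysis is descriptive. The change is still worth making, because the pilot exists to test recruitment and measurement for the main trial and the remedy is cheap.

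**What to change.** 1. In section 8.3 (timeline text and schedule footnote) and section 11.4, trigger the t1 questionnaires after the encounter in which the treatment choice is discussed, whether or not it ends in a decision. At minimum, apply this to control part 1: characteristics, knowledge, adherence, costs and quality of life.
2. Add one item for patient and professional: decision made, deferred, or not discussed. Report the number deferred or undecided per arm as a feasibility result.
3. If undecided patients complete the decisional conflict scale, report their scores separately from those of deciders.
4. Reconcile the schedule table with the follow-up sentence in section 8.3 on whether the scale is given at 3 and 9 months, and state the date from which those intervals run.

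The cost is a wording amendment and one extra item. The small downside is that some patients would answer the scale about a pending decision, which item 3 contains. The change does not give controls a baseline before the encounter.

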1. SAFETY REPORTING
   1. Temporary halt for reasons of subject safety

In accordance to section 10, subsection 4, of the WMO, the sponsor will suspend the study if there is sufficient ground that continuation of the study will jeopardise subject health or safety. The sponsor will notify the accredited METC without undue delay of a temporary halt including the reason for such an action. The study will be suspended pending a further positive decision by the accredited METC. The investigator will take care that all subjects are kept informed.

- 1. AEs, SAEs and SUSARs

The multistage SDM program will be implemented in two primary care practices in this pilot study. Although this is an intervention study, the intervention does not require the administration of any therapeutic agent. The PDA, as part of the multistage program, explicitly does not provide advice for a particular treatment. It aims to help patients with T2DM and HCPs to decide on the most suitable treatment. The direction for medication usage is at the discretion of a HCP in accordance with usual medical practice.

- - 1. Adverse events (AEs)

Adverse events are defined as any undesirable experience occurring to a subject during the study, whether or not considered related to the multistage SDM program for T2DM. Although an AE related to the multistage SDM program is not expected, all adverse events reported spontaneously by the subject or observed by the investigator or his staff will be recorded.

- - 1. Serious adverse events (SAEs)

A serious adverse event is any untoward medical occurrence or effect that

- results in death;
- is life threatening (at the time of the event);
- requires hospitalisation or prolongation of existing inpatients’ hospitalisation;
- results in persistent or significant disability or incapacity;
- is a congenital anomaly or birth defect; or
- any other important medical event that did not result in any of the outcomes listed above due to medical or surgical intervention but could have been based upon appropriate judgement by the investigator.

An elective hospital admission will not be considered as a serious adverse event.

The investigator must evaluate each SAE for causality and record causality for each event reported. The investigator will report all SAEs to the sponsor without undue delay after obtaining knowledge of the events.

The sponsor will report the SAEs through the web portal *ToetsingOnline* to the accredited METC that approved the protocol, within 7 days of first knowledge for SAEs that result in death or are life threatening followed by a period of maximum of 8 days to complete the initial preliminary report. All other SAEs will be reported within a period of maximum 15 days after the sponsor has first knowledge of the serious adverse events.

- - 1. Suspected unexpected serious adverse reactions (SUSARs)

Not applicable.

- 1. Annual safety report

Not applicable.

- 1. Follow-up of adverse events

All AEs will be followed until they have abated, or until a stable situation has been reached. Depending on the event, follow up may require additional tests or medical procedures as indicated, and/or referral to the general physician or a medical specialist.

SAEs need to be reported till end of study within the Netherlands, as defined in the protocol.

- 1. Data Safety Monitoring Board (DSMB) / Safety Committee

Not applicable.

1. STATISTICAL ANALYSIS
   1. Primary study parameter(s)

No substitution of missing or incomplete data will be done. The extent of missing data will be assessed, and reasons for missingness will be explored. Missing data patterns will be described to identify potential biases. Reporting and discussion of missing data will be included in the results to provide transparency and enable assessment of potential biases in the study.

Descriptive analysis will be conducted for quantitative data. Counts and percentages for non-continuous data and mean scores and standard deviations for continuous data will be calculated. This includes sociodemographic and clinical characteristics, primary outcomes, secondary outcomes, completion times of questionnaires, the prevalence of missing responses in the questionnaires, and estimates related to feasibility (e.g. recruitment rates). Descriptive analysis will be performed in Rstudio [46]. Descriptive statistics will be reported separately for each study aspect. No statistical analyses will be performed to determine the (cost-)effectiveness of the multistage SDM program since this is not the primary objective of the pilot study.

As to qualitative data, all interviews and focus groups will be audio-recorded and transcribed ad verbatim. Transcripts are analyzed in ATLAS.ti using thematic analysis with an inductive approach following three steps [47, 48]. First, the transcripts will be read and re-read in a process called ‘familiarization’. Second, phrases, sentences, and paragraphs with meaningful topics will be isolated and labeled by a code for each interview transcript. Two researchers will independently code part of the transcripts and compare and discuss codes for reflexivity, after which the remaining transcripts will be divided. Inter-coder reliability will be established and maintained throughout the coding process. Third, themes are developed by clustering codes with similar meanings or interrelations, to understand, interpret, and report the main insights flowing from the data. The insights gained by conducting interviews with patients with T2DM will be used to improve, where necessary, the understandability of the questionnaires used.

The data management process (i.e. data collection, data processing, data quality, and data analysis) and possible improvements thereof will be discussed with the research team in three 2-hour meetings during and after the completion of data analysis.

- 1. Secondary study parameter(s)

Not applicable

- 1. Other study parameters

Not applicable

- 1. Interim analysis (if applicable)

Not applicable

